## Abstract

**Background:**

Previous self-harm is one of the strongest predictors of future self-harm and suicide. Increased risk of repeated self-harm and suicide exists amongst patients presenting to hospital with high-risk self-harm and major self-harm repeaters. However, so far evidence-based training in the management of self-harm for mental health professionals is limited. Within this context, we aim to develop, implement and evaluate a training programme, **SAMAGH, S**elf-harm **A**ssessment and **M**anagement Programme for **G**eneral **H**ospitals in Ireland. SAMAGH aims to (a) reduce hospital-based self-harm repetition rates and (b) increase rates of mental health assessments being conducted with self-harm patients. We also aim to evaluate the training on self-harm knowledge, attitudes, and skills related outcomes of healthcare professionals involved in the training.

**Methods/design:**

The study will be conducted in three phases. First, the SAMAGH Training Programme has been developed, which comprises two parts: 1) E-learning Programme and 2) Simulation Training. Second, SAMAGH will be delivered to healthcare professionals from general hospitals in Ireland. Third, an outcome and process evaluation will be conducted using a pre-post design. The outcome evaluation will be conducted using aggregated data from the National Self-Harm Registry Ireland (NSHRI) on self-harm repetition rates from all 27 public hospitals in Ireland. Aggregated data based on the 3-year average (2016, 2017, 2018) self-harm repetition rates prior to the implementation of the SAMAGH will be used as baseline data, and NSHRI data from 6 and 12 months after the implementation of SAMAGH will be used as follow-up. For the process evaluation, questionnaires and focus groups will be administered and conducted with healthcare professionals who completed the training.

**Discussion:**

This study will contribute to the evidence base regarding the effectiveness of an evidence informed training programme that aims to reduce repeated hospital self-harm presentations and to improve compliance with self-harm assessment and management. This study is also expected to contribute to self-harm and suicide training with the possibility of being translated to other settings. Its feasibility will be evaluated through a process evaluation.

## Background

Self-harm and suicide are major public health concerns. Worldwide over 800,000 people die due to suicide every year and is the second leading cause of death among young people [1]. For each suicide, there are more than 20 suicide attempts [1]. In 2018, the National Self-Harm Registry of Ireland (NSHRI) recorded 12,588 hospital presentations due to self-harm nationally, involving 9785 individuals [2]. Compared to 2017, self-harm hospital presentations in Ireland have increased by 7%. Furthermore, over 22% of patients repeated self-harm. Similar increasing trends have followed worldwide [3], although certain decreasing rates have been reported [4]. Furthermore, there was a significant increase in certain highly lethal self-harm methods used, such as attempted hanging, which increased by 24% from 2017 [2]. Self-harm is one of the strongest risk factors for both non-fatal self-harm repetition and suicide, with evidence indicating certain groups being more prone to repeat self-harm and/or die by suicide (e.g. men, young people, older age groups, people engaging in more lethal self-harm methods and those with a history of 4 or more previous presentations) [5, 6].

Although research indicates that most self-harm episodes occur within the community, a significant amount of presentations will occur in hospital settings, creating the opportunity for intervention when assessing and managing self-harm patients [6–8]. Evidence regarding hospital-based interventions to reduce self-harm show promising findings [7, 9, 10]. However, despite evidence indicating improved patient outcomes following assessment of self-harm patients [10, 11], many of these patients still leave hospital without an assessment [2, 12]. Moreover, the majority of hospital-based interventions for self-harm have been conducted with all self-harm patients rather than targeted subgroups [7, 9, 10]. There is increased risk of suicide among those engaging in highly lethal self-harm methods [13] and those with repeated previous self-harm attempts [14]. Previous research into these two subgroups has identified particular and distinct phenotypes for each, requiring specific interventions [15, 16]. Major self-harm repeaters have psychiatric history, including personality and mood disorder diagnoses, as well as a history of physical, emotional or sexual abuse, and method escalation. While high-risk self-harm patients have increased psychiatric and physical comorbidities, substance abuse, and are more often male. The available self-harm intervention programmes refer to the overall self-harm population, and therefore, they may not adequately address the needs of these specific subgroups. Moreover, healthcare professionals face multiple challenges in managing self-harm patients in general and high-risk subgroups in particular [17].

To date there are no evidence-based interventions for supporting these subgroups of patients. It is within this context that the SAMAGH training programme has been developed.

### Aim

In this study, we aim to implement and evaluate an evidence informed training programme, **SAMAGH, S**elf-harm **A**ssessment and **Ma**nagement Programme for **G**eneral **H**ospitals in Ireland. SAMAGH aims to (a) reduce hospital-based self-harm repetition rates overall and amongst the two subgroups and (b) increase rates of mental health assessments being conducted with self-harm patients. This study will address a number of specific objectives:
Assess the impact of the SAMAGH training for health professionals in hospital settings on overall repeated self-harm rates as well as in the two subgroups of high-risk patients.Determine whether the SAMAGH training results in increased rates of mental health assessments being conducted with self-harm patients.Conduct a process evaluation to understand the feasibility of implementing the SAMAGH training and its effect on health professionals’ knowledge, attitudes and skills on assessment and management of self-harm patients.

## Methods/ design

SAMAGH is a three-phase study as reflected in Fig. 1. The three methods of the phases of development, implementation, and evaluation are described in detail below.

**Fig. 1 Fig1:**
[figure not shown]
Description of the three-phase SAMAGH study

### Phase 1: development of the SAMAGH training Programme

SAMAGH was developed based on information obtained from two previous studies on specific predictive factors for repeated self-harm and suicide among high-risk groups: SSIS-ACE (Psychological, psychiatric and work related risk factors associated with suicide in Ireland: a case control study) and IMPRESS (Improving Prediction and Risk Assessment of Self-harm and Suicide: an in-depth interview study) [18]. Extensive literature reviews, consultation with different expert groups including relevant groups of clinicians (psychiatrists, psychologists, and nurses), academics, and reviews of existing manuals for self-harm and suicide informed the development of SAMAGH.

Simulation training is a core component of SAMAGH. Simulation-based learning is a learning method that can develop health professionals’ knowledge, skills, and attitudes, whilst protecting patients from unnecessary risks [19]. Simulation training has been increasingly used in medical training, but less frequently in mental health training. It is the educational practice of recreating patient scenarios in safe environments using trained actors and technology, followed by debriefing to reinforce learning [20]. Through the use of actors, high-fidelity patient scenarios can be enacted and health professionals have the opportunity to practice and enhance the development of therapeutic alliance which is essential in mental health care [20].

We conducted an extensive review of the existing evidence of simulation training on self-harm and suicide prevention. Only five peer reviewed published studies were available, addressing self-harm/suicide related knowledge and attitude related outcomes [21–23], feasibility of the training [23], teaching learning outcomes [24], and improving gatekeeper behaviour for suicide prevention [25]. The simulation training methods varied from role-play sessions with virtual patients [23], people with lived experience of mental illness [21], simulated emergency medical scenarios with high fidelity mannequins and structured reflective debriefing [22], online role-play simulations with use of emotionally responsive avatars [25], and training using theatre students as simulated standardised patients [24]. The review did not reveal any studies that evaluated a simulation training programme specific to self-harm subgroups. Hence, we developed an evidence informed simulation-based intervention for self-harm assessment and management.

SAMAGH consists of two training sections. First, an E-Learning programme, where across eight comprehensive modules, health professionals will extend their knowledge of the nature and management of self-harm and suicide, with a focus on the two previously mentioned high-risk groups. The second part of the programme comprises a two-day face-to-face interactive training course, including simulation training. Figure 2 provides a description of the components of the SAMAGH training.

**Fig. 2 Fig2:**
[figure not shown]
Description of SAMAGH

The subgroups of self-harm patients are defined as follows:
Major repeater self-harm patients with a history of four or more previous self-harm presentations to hospital prior to their index self-harm presentation.High-risk self-harm: (a) highly lethal self-harm presentations, and/or (b) presentations with high levels of suicidal intent. The same criteria used by Arensman et al [18, 26] will be used to define high-risk self-harm, which is a combination of a highly lethal methods, medical severity and clinical impression of high suicide intent (See Additional File 1).

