#### Simulation training

The simulation training will be held at the ASSERT centre in University College Cork. During the first few hours, participants will receive a masterclass lecture to re-inforce the knowledge from the E-learning Programme, with a specific focus on conducting a biopsychosocial assessment. A total of three patient scenarios will be given to participants for them to role play during the two-day training. The three patient scenarios include scenarios representing high-risk self-harm patients, major self-harm repeaters, and challenging behaviour patients. Participants will learn how to best assess and manage these self-harm patients through simulation training. The three patient scenarios will be played by actors who have had previous experience in medical simulation training and who received in-house inductions on the different patient roles to be played.

Facilities from the ASSERT centre include two rooms which simulate a hospital Emergency Department setting and have two-way mirrors (see Additional File 2). Participants will be divided into groups of two, in order to optimise learning in smaller groups. All participants will be individually involved in the simulation training, playing out the three patient scenarios each. The remaining participants will observe and learn from their colleagues who are completing the simulation training, and will be accompanied by facilitators/reviewers, who will grade participant’s simulation training. At the end of each simulation training, the facilitators/reviewers will provide feedback to the participant and group, making it a group learning exercise. Facilitators for the simulation training include self-harm and suicide prevention experts, including consultant psychiatrists, academic professors and the national clinical lead and head of nursing for the national clinical programme of self-harm assessment and management of patients presenting to emergency departments.

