#### Outcome evaluation

An outcome evaluation study will be conducted using a pre-post design. NSHRI aggregated data at a national level across the 27 hospitals in Ireland will be used, based on the 3 year average before the implementation of the SAMAGH training programme and 6 and 12 months after implementation of the programme. Outcomes to be included are: (a) hospital self-harm repetition rates, and (b) assessment rates following the hospital self-harm presentation. Aggregated data from the NSHRI allows for the analysis of hospital self-harm repetition rates of subgroups of self-harm patients, including patients with a history of 4 or more previous hospital self-harm episodes and those presenting to hospital following high-risk self-harm.

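### High-risk subgroup membership rests partly on clinical impression of intent, which the training may shift, so the before/after comparison in that one subgroup is open to classification bias of unknown size and direction

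*Protocol article*

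**What the plan says.** The subgroup definitions in the protocol article (Phase 1, under Fig. 2) introduce the group as "High-risk self-harm: (a) highly lethal self-harm presentations, and/or (b) presentations with high levels of suicidal intent". The next sentence says that criteria from earlier work will be used, "which is a combination of a highly lethal methods, medical severity and clinical impression of high suicide intent", and sends the reader to Additional File 1, which is not shown. The other subgroup is a count: "Major repeater self-harm patients with a history of four or more previous self-harm presentations to hospital prior to their index self-harm presentation".

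The Outcome evaluation section says that aggregated registry data allow repetition rates to be analysed for major repeaters "and those presenting to hospital following high-risk self-harm". The comparison is pre-post without a control group: a three-year average before implementation, against 6 and 12 months after it. The Statistical analysis section uses Poisson regression for repetition overall and in the two subgroups. The adjustment variables it names concern services, hospital type and staff trained. None captures a change in who is classed as high-risk.

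On the training, the Simulation training section describes a high-risk patient scenario among others and says: "Participants will learn how to best assess and manage these self-harm patients through simulation training". The Aim section says that SAMAGH should also "increase rates of mental health assessments being conducted with self-harm patients", and the Background notes that "many of these patients still leave hospital without an assessment".

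**The concern.** One route into the high-risk group runs through a clinician's judgement of intent, and the intervention is directed at the clinicians who assess these patients. If the training works as hoped, more patients are assessed, and by staff who may judge intent differently. The set of patients labelled high-risk after implementation could then differ from the set labelled so in 2016–2018, even if no patient's risk of repeating had changed. Success on the assessment outcome could alter the denominator of the subgroup repetition outcome.

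Reducing repetition in the high-risk group is a stated aim. A shift in case mix could produce an apparent benefit, hide a real one, or suggest harm. Without a control group, nothing in the planned comparison separates such a shift from a training effect. Adjusting for staff trained would not remove it, because relabelling could be greatest where most staff were trained and so resemble a dose response.

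**Working it through.** **No plan figure to reproduce.** The documents give no size, repetition rate or intent-only share for the high-risk subgroup. The one related figure that I borrow does reproduce: 1322/9103 = 14.5% of all patients repeated in 2017 (Sample size and power calculation). Every other input below is an assumption. The 12% core rate is the plan's anticipated starting rate for repetition, used here as a stand-in for the subgroup.

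**Formula.** Let p_core be the repetition rate of patients classed high-risk under the old practice, g the relative growth of the subgroup through extra labels, and p_added the rate in the added patients. With no true effect:

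observed rate after = (p_core + g × p_added) / (1 + g)

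**Core 12%, added patients at 8%:**
- g = 10%: (0.12 + 0.008)/1.10 = 11.6%
- g = 25%: (0.12 + 0.020)/1.25 = 11.2%
- g = 50%: (0.12 + 0.040)/1.50 = 10.7%

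**Core 12%, added patients at 20%:**
- g = 10%: (0.12 + 0.020)/1.10 = 12.7%
- g = 25%: (0.12 + 0.050)/1.25 = 13.6%
- g = 50%: (0.12 + 0.100)/1.50 = 14.7%

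If p_added = p_core, the shift is exactly zero for any g.

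**Higher core rate (25%), added patients at the all-patient 14.5%:**
- g = 10%: 0.2645/1.10 = 24.0%
- g = 20%: 0.2790/1.20 = 23.3%
- g = 30%: 0.2935/1.30 = 22.6%

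This is a relative fall of about 4% to 10%. The 25% and the 10–30% growth are for illustration only.

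**Labels withdrawn instead of added.** If training removed 10% of the labels, from patients repeating at 8%, a 12% subgroup would move to (0.12 − 0.10 × 0.08)/0.90 = 12.4%. The sign depends on which way the labels move as well as on the rates.

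**Chance of a false significant change.** I used a two-sided pooled two-proportion z-test at 0.05, core rate 12%, no true effect, one year of 9103 patients before, and the subgroup enlarged by g after.
- Subgroup 10% of patients, g = 25%, added at 8%: n = 910 and 1138, difference 0.008, SE 0.0142, chance 8.7%
- Subgroup 20%, g = 50%, added at 8%: n = 1821 and 2731, difference 0.0133, SE 0.0095, chance 29%
- Subgroup shares of 5–20%, g of 10–50%, added at 6–10%: about 5% to 57%, against a nominal 5%

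**Against the planned effect.** For relabelling alone to turn 12% into 8%, g = (0.12 − 0.08)/(0.08 − p_added). With p_added = 4% the subgroup must double (g = 100%); with 6% it must triple (g = 200%). Relabelling is therefore unlikely to imitate the whole planned fall, but it could contribute to a smaller one. The protocol does not specify the 12% to 8% target for this subgroup.

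**The case against.** The strongest case against is that the documents show a route, not an effect. No section says that the training alters the threshold for judging intent as high, who forms the impression, or that the impression depends on the mental health assessment counted as an outcome. Additional File 1 may fix the coding, and if the registry builds the subgroup from method or severity alone, the problem is absent. Reach is also thin: 40 to 50 volunteers over 27 hospitals is 1.5 to 1.9 per hospital (40/27, 50/27), which makes large national label growth hard to picture. All of this stands, and it limits the point to a possibility.

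It does not remove the point. The article itself names clinical impression as a criterion. A fixed rule applied to a recorded impression would inherit any change in that impression. The plan also relies on the same trainees to move national repetition and assessment rates, so their reach cannot be assumed enough for benefit yet negligible for labelling.

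A reader might also infer that *and/or* and *combination* contradict each other. That goes too far: *combination* can mean a composite that draws on several elements. The wording is loose rather than shown to be wrong.

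Replacing the adopted definition outright would be a real trade-off. It would drop the intent-only patients whom the definition deliberately includes, and their share is not given.

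**Conclusion.** The concern holds as a risk of bias in one subgroup comparison. Membership of the high-risk group may be altered by the intervention under test, and the protocol names no safeguard. A reader might infer that the training does change the label, or that patients before and after are not comparable. The documents do not support either as fact, nor a bias in one particular direction. The shift is zero if added patients repeat at the core rate, downward if they repeat less often, and upward if they repeat more often.

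On the assumed inputs with a 12% core rate and 10–50% growth, the subgroup rate moves to between 10.7% (added at 8%) and 14.7% (added at 20%) with no true effect. These are illustrations, not estimates. The point does not extend to overall repetition, which does not use the label, or to major repeaters, who are defined by a count of previous presentations.

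**What to change.** - Keep the adopted definition. Add a pre-specified analysis of the high-risk subgroup using only criteria that do not depend on clinician judgement, applied identically to 2016–2018 and follow-up records. Method lethality is available: the Background cites registry data on highly lethal methods such as attempted hanging. Add medical severity if the registry holds it.
- Report the number and proportion of patients classed high-risk in each period under both definitions.
- Interpret a change in the subgroup as a training effect only if the two analyses agree. Agreement answers this objection, not the other limits of an uncontrolled design.
- State in the subgroup definitions whether the criteria are combined by *and* or by *or*, and how intent is coded in each period.

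The cost is a little more analysis work and some wording. It is best settled before the aggregates are drawn, since aggregated data may not allow reclassification later. The added analysis leaves out patients identified by intent alone, so a disagreement between the two could also reflect a real difference in those patients.

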### Phase 2: implementation of the SAMAGH training Programme

An invitation to participate in SAMAGH will be sent to a representative group of 40 to 50 health professionals (Clinical Nurse Specialists, Non-Consultant Hospital Doctors, Psychiatry Registrars, Clinical Psychologists, Psychiatrists, among others) working across the 27 public hospitals in Ireland. Given that the SAMAGH Training Programme does not have a special focus on children, children’s hospitals will not be included in the recruitment of health professionals. Each group of health professionals will have representatives from a range of different hospitals across Ireland. Attending the SAMAGH training is not compulsory for health staff. SAMAGH will be delivered to groups of 8–10 participants, and there will be approximately five groups in total. It is expected that health professionals who complete the training will incorporate the learned skills and knowledge in their daily practice with self-harm patients.

#### E-learning Programme

One week prior to the face-to-face simulation training, participants will receive the details for the E-learning Programme via e-mail. The E-learning Programme is comprised of eight modules and will take approximately 2 to 3 h to complete. The E-learning Programme includes multiple-choice questions at the end of each module, and participants must obtain a 70% score overall to successfully complete the programme. Participants must have successfully completed the E-learning Programme prior to attending the Simulation Training as key concepts will have been introduced and reinforced to participants.

#### Simulation training

The simulation training will be held at the ASSERT centre in University College Cork. During the first few hours, participants will receive a masterclass lecture to re-inforce the knowledge from the E-learning Programme, with a specific focus on conducting a biopsychosocial assessment. A total of three patient scenarios will be given to participants for them to role play during the two-day training. The three patient scenarios include scenarios representing high-risk self-harm patients, major self-harm repeaters, and challenging behaviour patients. Participants will learn how to best assess and manage these self-harm patients through simulation training. The three patient scenarios will be played by actors who have had previous experience in medical simulation training and who received in-house inductions on the different patient roles to be played.

Facilities from the ASSERT centre include two rooms which simulate a hospital Emergency Department setting and have two-way mirrors (see Additional File 2). Participants will be divided into groups of two, in order to optimise learning in smaller groups. All participants will be individually involved in the simulation training, playing out the three patient scenarios each. The remaining participants will observe and learn from their colleagues who are completing the simulation training, and will be accompanied by facilitators/reviewers, who will grade participant’s simulation training. At the end of each simulation training, the facilitators/reviewers will provide feedback to the participant and group, making it a group learning exercise. Facilitators for the simulation training include self-harm and suicide prevention experts, including consultant psychiatrists, academic professors and the national clinical lead and head of nursing for the national clinical programme of self-harm assessment and management of patients presenting to emergency departments.

